### Blinding

2.11

Trial participants will be blinded to treatment allocation. ESWT is not routinely used in DFU care and therefore it is highly unlikely that participants will have experienced ESWT before and be able to identify the sham. In addition, many of the participants will have peripheral neuropathy so will not be able to feel any sensations associated with ESWT.

The outcome assessors, who are experts in wound care, will assess for DFU healing. They will be blinded to the participants treatment allocation. The outcome assessors will not be involved in randomisation or delivery of ESWT. Unblinding will be permissible if there is an adverse event related to the trial intervention. This will be achieved by contacting the Principal Investigator who will determine if the event was related to the intervention and, if so, will inform the clinical team and patient of the arm allocation. Participants can be unblinded following the 24‐week F2F follow‐up visit if they chose.

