All participants will receive standard care outlined by the NICE and IWGDF guidance [15, 16, 30, 31]. This will include regular dressing changes, sharp debridement, offloading footwear, control of infection and optimisation of blood glucose. Specific aspects of standard care participants receive will be reported. There will be no restrictions on concomitant care or interventions.

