### Allocation

2.10

Participants will be randomised on a 1:1:1 allocation ratio to sham ESWT, low dose ESWT and high dose ESWT. Participants will be stratified by ulcer size (< 1 and ≥ 1 cm^2^) and ischaemia (ABPI 0.7–0.79 and ≥ 0.8; OR absolute toe pressure 50–59 and ≥ 60 mmHg). These two factors are predictive of healing [39, 40]. Stratified block randomisation with randomly varying block sizes of 3 and 6 will be used. Randomisation will be performed using an online randomised tool hosted at York Randomisation Service, York Trials Unit. The site researcher will enter the participants details into the online tool. The York Trials Unit trial manager, Principal Investigator and the site researcher will then receive an email with the participant's trial arm allocation.

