Health resource use											
Number of outpatient appointments					X	X	X	X			
Number of GP appointments					X	X	X	X			
Number of hospital admissions					X	X	X	X			
Length of stay					X	X	X	X			
Number of practice nurse appointments					X	X	X	X			
Number of district nurse appointments					X	X	X	X			
Number of podiatrist appointments					X	X	X	X			
Number of prescriptions					X	X	X	X			
Number of operations					X	X	X	X			
Ulcer healing					X	X	X	X	X	X	X
Adverse events			X	X	X	X	X	X	X	X	X
Qualitative interview	X^c^			X^d^	X^d^	X^d^	X^d^	X	X^d^	X^d^	

Abbreviations: ABPI: ankle brachial pressure index; BMI: body mass index; DFS‐SF: diabetic foot ulcer scale – short form; DFU: diabetic foot ulcer; EQ5D5L: EuroQol 5‐dimensions 5‐levels; ESWT: extracorporeal shockwave therapy; GP: general practitioner; SINBAD: site ischaemia neuropathy bacterial infection area and depth score; WIfI: wound ischaemia foot infection stage.

^a^
Every 2 weeks between finishing ESWT and the 24‐week follow‐up visit.

^b^
If the patient reports the ulcer is healed, repeated 2 weeks later to ensure the DFU remains healed.

^c^
If the eligible patient declines trial participation.

^d^
If the participant decides to withdraw from the trial before the 24‐week follow‐up visit.

Health‐related quality of life will be measured using EuroQol 5D‐5L (EQ‐5D‐5L), diabetic foot ulcer scale short form (DFS‐SF) and Wound‐Qol‐14. EQ‐5D‐5L will be used to aid economic evaluation of ESWT [42, 43, 44]. DFS‐SF is a disease‐specific validated tool that measures health‐related quality of life in participants with a DFU [45]. Wound‐Qol‐14 will be validated during the pilot RCT and is hypothesised to have a higher completion rate than DFS‐SF as it is shorter (14 items versus 29 items). The tool has been validated in a population with chronic wounds, which included patients with DFUs [46, 47].

Participants can withdraw from the intervention, F2F follow‐up, telephone follow‐up or completely withdraw from the trial. Consent will be sought to use of the data already collected and to continue collecting data from routine medical records. If a patient is lost to follow‐up, data will be collected from routine medical records.

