### Harms

2.17

All side effects will be recorded during the pilot RCT. The expected transient side effects of ESWT are mild pain, burning sensation, itchiness and erythema around the ulcer. The standard definitions of adverse event (AE), serious adverse event (SAE), unexpected and related will be used [51]. All AEs and device failures will be recorded. All SAEs will be reported to the Principal Investigator (PI) within 24 h of the event occurring. The PI will report SAEs to the Sponsor and Research Ethics Committee (REC), following Health Research Authority (HRA) guidance.

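### The unblinding rule in 2.11 rests on relatedness alone, so as written it can permit unblinding for mild, expected effects of ESWT, more often in the active arms

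*Protocol article*

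**What the plan says.** Section 2.11 (Blinding) sets the trigger: "Unblinding will be permissible if there is an adverse event related to the trial intervention". The route is "contacting the Principal Investigator who will determine if the event was related to the intervention"; the text continues "if so, will inform the clinical team and patient of the arm allocation". Apart from this, participants may choose to learn their arm after the 24-week face-to-face visit.

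The person judging relatedness is not blinded. Under section 2.10 (Allocation), the "Principal Investigator and the site researcher will then receive an email" giving the participant's arm.

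Section 2.17 (Harms) states: "The expected transient side effects of ESWT are mild pain, burning sensation, itchiness and erythema around the ulcer". It applies the standard definitions of adverse event and of related, and does not set these effects apart. Tables 2 and 3 list side effects of ESWT and adverse events on separate rows. Side effects are collected at the three treatment sessions, adverse events throughout follow-up.

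Two other statements bear on the consequences. On background treatment, section 2.5 says: "There will be no restrictions on concomitant care or interventions". On the healed visit, footnote b of Table 3 says: "If the patient reports the ulcer is healed, repeated 2 weeks later to ensure the DFU remains healed".

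**The concern.** A code-break rule normally protects the blind unless there is a reason to know the allocation. This one asks only whether the event was caused by the intervention. Seriousness, severity, expectedness and the need to know the arm do not enter. The effects named in 2.17 are attributed to ESWT by the protocol itself, so if they count as adverse events they will readily be judged related.

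The sham arm receives an audio recording and no shockwaves, and the Principal Investigator, who decides relatedness, knows who is on sham. Events judged related should therefore be less common on sham, and any loss of blinding would be uneven between arms.

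Those told are the patient and the clinical team. The patient completes the quality-of-life scales and, by reporting closure, prompts the healed visit. The clinical team gives background care without restriction. The Discussion names non-blinding of participants and assessors as a weakness of earlier ESWT trials that this pilot is meant to address, and the pilot's methods are intended to carry over to the definitive trial.

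**Working it through.** The plan states no figure on this point, so the check is mainly a reading of the sections side by side.

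1. **Trigger.** Section 2.11 requires an adverse event and relatedness, and nothing else. Severity does appear in 2.14 (events reported by type and severity) and seriousness in 2.16 (stop for related serious adverse events). Neither is carried into 2.11.
2. **Consequence.** The rule is permissive at the start, because someone must contact the Principal Investigator. After a finding of relatedness it becomes directive: the Principal Investigator "will inform the clinical team and patient of the arm allocation".
3. **Reach.** Section 2.17 lists mild pain, burning, itch and erythema as expected of ESWT and adopts standard definitions with no exclusion. The separate rows in Tables 2 and 3 point the other way, but no sentence says that a side effect is not an adverse event for the purpose of 2.11. The text leaves this open.
4. **Asymmetry.** Section 2.5 gives sham the same ulcer preparation and paddle contact but no shockwaves. Events caused by shockwaves cannot arise on sham. Events caused by cleansing, debridement, film or paddle contact can, so the sham rate need not be zero.
5. **Timing.** All three sessions fall within 7 ± 2 days. Unblinding for a session effect could therefore precede the quality-of-life assessments after session 3 and at weeks 6, 12 and 24.

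**Illustration only.** The documents give no event rate, so the rates below are assumptions. They also assume that every related event leads to a request, which overstates the count at any given rate. With 90 participants allocated 1:1:1, about 60 are active and 30 sham. Let p be the assumed proportion of active participants with an event judged related.

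- Expected number unblinded on active = 60 × p
- Chance of at least one = 1 − (1 − p)^60
- Active share of unblindings, if 2% of sham also have a related event (30 × 0.02 = 0.6) = 60p / (60p + 0.6)

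| Assumed p | Expected, active | Chance of at least one | Active share with 2% on sham |
|---|---|---|---|
| 2% | 1.2 | 0.70 | 67% |
| 5% | 3 | 0.95 | 83% |
| 10% | 6 | 0.998 | 91% |
| 20% | 12 | 1.00 | 95% |
| 30% | 18 | 1.00 | 97% |

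The 67% in the first row is simply the 60:30 allocation at equal rates, so it shows no asymmetry. The imbalance appears only as the active rate rises above the sham rate. The table shows how the result depends on the unknown rate. It does not estimate what will happen.

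**The case against.** The best defence has four parts.

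- **The rule is permissive.** Unblinding must be requested, and nothing suggests a request for every transient itch. This stands. A reader might infer that the rule unblinds automatically, and the text does not support that.
- **Side effects and adverse events are recorded separately.** Separate rows in Tables 2 and 3, and separate sentences in 2.17, suggest that expected transient effects may be meant to sit outside the unblinding rule. This is a fair reading, but the standard definitions in 2.17 exclude nothing, so it remains an ambiguity and not an answer.
- **Neuropathy blunts sensation.** Section 2.11 says many participants will not feel ESWT. Three of the four listed effects (pain, burning, itch) are sensory. This lowers the likely rate but does not apply to erythema.
- **The consequences are bounded.** Healing assessors are not among those told. Healing must be confirmed two weeks apart by a blinded assessor, and it is also assessed at the 6-, 12- and 24-week visits whatever the patient reports. The primary outcome is deliverability, and secondary outcomes are reported without testing. All of this stands.

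Two stronger readings are tempting. One is a firm count, such as 6 to 18 of 60 active participants against none on sham. The documents give no rate for either arm, so that count has no documentary basis. The other is that an event judged unrelated leaves the treating team no route to the code. The article condenses a full protocol that may hold the emergency procedure, so its absence here shows nothing.

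**Conclusion.** The point holds in limited form. As written, 2.11 makes relatedness the only stated condition for unblinding before week 24. Read with 2.17, it can on request permit the patient and clinical team to be told the arm for a mild expected effect, more often in the active arms.

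The size cannot be stated, because no rate of related events or of requests is given. The greater frequency in the active arms is an inference from the sham delivering no shockwaves and from the Principal Investigator, who decides relatedness, knowing the arm; the protocol does not state it. The exposure is to patient-reported quality of life, the timing of patient-triggered healed visits and concomitant care, in those participants who are actually unblinded. Blinded confirmation of healing is not directly affected. The wording should be corrected, since it is cheap to do and the rule may be carried into the definitive trial, but it does not undermine the pilot.

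**What to change.** Reconcile 2.11 with 2.17 and Tables 2 and 3:

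1. State that the expected transient side effects listed in 2.17 are not, on their own, grounds for unblinding.
2. Base code-breaks on a need to know the allocation, and not on relatedness alone. Where that threshold lies is for the trial team to set.
3. Log each code-break with arm and date, and report the log by arm.

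This costs a few sentences in the protocol and a code-break entry on the case report form. The small downside is that some participants with mild effects will learn their arm only after the 24-week visit.

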### Data Monitoring

2.16

Eligibility rates, recruitment rates, treatment adherence, follow‐up adherence and adverse events will be reviewed by the trial management group (TMG) monthly and the trial steering committee (TSC) bi‐annually. The TSC will use Stop/Go criteria to decide whether to continue the pilot trial or pause recruitment and amend trial processes. The Stop/Go criteria [50] are:
–Green (continue): > 60% recruitment, adherence to treatment arm and follow‐up attendance per month.–Amber (continue, review trial processes): 30%–60% recruitment, adherence to treatment arm and follow‐up attendance per month.–Red
○< 30% (Stop, amend trial processes) recruitment, adherence to treatment arm and follow‐up attendance per month.○Serious adverse events related to ESWT (stop, review).

The auditing of the trial processes will take place by independent auditors from the Sponsor's Research, Development and Innovation (RD&I) Department.

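### The Principal Investigator is sent every allocation and also judges whether adverse events are related, so causality labels and the decision to unblind are made with knowledge of the arm

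*Protocol article*

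**What the plan says.** Section 2.10 (Allocation) describes what follows each randomisation: "The York Trials Unit trial manager, Principal Investigator and the site researcher will then receive an email with the participant's trial arm allocation".

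Section 2.11 (Blinding) blinds the participants and the people who judge healing: "The outcome assessors, who are experts in wound care, will assess for DFU healing". It then sets the condition for breaking the blind during follow-up: "Unblinding will be permissible if there is an adverse event related to the trial intervention". The mechanism is: "This will be achieved by contacting the Principal Investigator who will determine if the event was related to the intervention". If the answer is yes, the Principal Investigator tells the clinical team and the patient which arm it was. Separately, participants may ask to be unblinded after the 24-week visit.

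Section 2.17 (Harms) routes all serious adverse events to the Principal Investigator, who passes them to the sponsor and the ethics committee.

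Section 2.16 (Data Monitoring) lists among the Red criteria "Serious adverse events related to ESWT (stop, review". On who applies the criteria it says: "The TSC will use Stop/Go criteria to decide whether to continue the pilot trial or pause recruitment and amend trial processes".

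**The concern.** A sham arm helps in judging harms because the person deciding causality cannot tell which participants received shocks. Here that person can. An active-arm event may be called related because shocks were given, and the same event in a sham participant called unrelated because none were. An investigator might also lean the other way and under-attribute events in the active arms. The plan guards against neither.

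Three things depend on the label:

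- **The causality record itself.** The expected effects in section 2.17 (mild pain, burning, itching, redness) are non-specific. They could follow the cleansing, debridement, film, gel and paddle contact that section 2.5 gives to all arms.
- **Unblinding.** Because disclosure requires a finding of relatedness, a leaning in that finding makes disclosure more frequent in some arms than in others. Concomitant care is unrestricted (section 2.5) and quality of life is patient-reported (section 2.12), so unequal unblinding could reach secondary outcomes.
- **The Red safety criterion.** It is conditional on relatedness and states no minimum count.

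The Discussion says that earlier evidence was marked down partly for inadequate blinding and that this pilot is meant to address that. A process tested here is likely to carry into the definitive trial.

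**Working it through.** The plan gives no figure to reproduce. The check is a cross-reading of who knows the arm, who judges causality, and what uses that judgement.

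1. **Who knows the arm.** Section 2.10 names three recipients of every allocation: the trials unit's trial manager, the Principal Investigator and the site researcher.
2. **Who judges relatedness.** Section 2.11 names the Principal Investigator. No other role is given this task anywhere in the article. The blinded assessors' stated task is healing (sections 2.11 and 2.12).
3. **Combining 1 and 2.** Relatedness is judged by someone who holds the allocation. Both halves are stated outright.
4. **Does the judgement control unblinding?** Yes, for event-driven unblinding: section 2.11 makes disclosure to patient and clinical team follow from it.
5. **Does it control the safety criterion?** Section 2.16 makes relatedness to ESWT the condition but does not say whose assessment the steering committee uses. The Principal Investigator is the only role named for causality and receives every serious event report. The link is a strong inference.
6. **Does it enter the between-arm harm summaries?** No. Section 2.14 reports events by type and severity, as a total rate and as events per patient, for each arm. Relatedness is not mentioned. The Discussion judges safety by numbers of serious adverse events, again without regard to relatedness.
7. **Is the sham background still recorded?** Yes. Section 2.17 records all side effects, all adverse events and device failures. Section 2.12 records side effects at each session, partly by report from blinded participants.

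**Illustration of size (assumed inputs).** Let p be the proportion in each arm with an event that a blinded clinician would call related. Let a and s be the probabilities that an assessor who knows the arm gives that label to such an event in an active arm and in the sham arm.

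- Spurious difference in labelled events = p × (a − s).
- Participants per arm from the target of 90 (section 2.8): 90 / 3 = 30.
- Assume p = 10%: 0.10 × 30 = 3 participants per arm.
- With a = 1 and s = 1 (knowledge of the arm has no influence): 10% × (1 − 1) = 0 points.
- With a = 1 and s = 0 (no sham event is ever called related): 10% × (1 − 0) = 10 points, that is 10% against 0% where blinded labelling would give 10% against 10%.

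With a = 1 the range is 0 to 10 points, and the upper end always equals p. If a is below s, the sign reverses. None of p, a or s is in the documents, and the calculation describes labels, not a comparison that section 2.14 plans.

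**The case against.** The strongest reply is that the label has little to act on. The harm summaries are all-cause, safety is read from counts of serious events, and the sham background rate is collected whatever anyone decides about causality. A reader might infer from the overlap of roles that the comparison of harms between arms, or the safety reading in neuro-ischaemic and infected ulcers, is biased. The documents do not support that: neither uses relatedness.

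A reader might also infer that the Principal Investigator alone can stop the trial. The text does not support that either. The steering committee applies the criteria, the Red safety item provides for review, and the committee and the management group see adverse events without a restriction to related ones.

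Nor does it follow that a sham event can never be called related. Section 2.11 speaks of the trial intervention, and the sham procedure is described under Interventions and includes physical contact with the ulcer. Near-zero attribution in the sham arm is more plausible for the narrower wording of section 2.16, which refers to ESWT.

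Two practical points stand. The Principal Investigator may need allocations, for example if that person delivers treatment; the article says only that a trained researcher does so. And the primary outcome is deliverability, whose component ratios do not use causality labels.

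It can also be said that a condensed article leaves safety procedures to the full protocol. That would answer a complaint about missing detail. Here the article itself names both the recipient of the allocation and the person who decides causality, and they are the same role.

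**Conclusion.** The point holds in a limited form. Causality labels and event-driven unblinding are decided by someone who knows the arm; this rests on direct statements in sections 2.10 and 2.11. The relatedness input to the Red criterion is very probably decided in the same way; this rests on no other role being named for the task.

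The all-cause summaries by arm, the counts of serious events and the deliverability ratios do not depend on the judgement. The double-blind description, as the article applies it to participants and healing assessors, is not contradicted.

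The size cannot be estimated from the documents. The 10-point figure is an upper bound under an assumed 10% event rate and complete relabelling in the sham arm, not a forecast. Differential unblinding, and any effect of it on quality of life or concomitant care, is a reasoned possibility and not a demonstrated effect. The change is worth making because it is cheap and concerns a process that the pilot is meant to test.

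**What to change.** Amend section 2.11 so that relatedness is judged and recorded, before any allocation is disclosed, by a clinician already in the trial who does not hold allocations. The Principal Investigator or the trial manager then discloses the arm if needed. State in section 2.16 that this blinded judgement is the one supplied to the steering committee for the Red criterion.

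Two candidates exist:

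- **The Chief Investigator**, who is not on the allocation email. Section 3.5 gives that role access to identifiable data and no blinding status is stated, so the sponsor must first confirm that the role has no access to allocations.
- **One of the blinded wound assessors**, provided that the assessor is not told the arm afterwards. Otherwise the blinded assessment of healing is lost for that participant.

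Taking the Principal Investigator off the allocation email is optional and depends on whether that person delivers treatment. The main change does not require it.

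The cost is one sentence in section 2.11, a matching clause in section 2.16, and one extra contact for each event that needs attribution. If one of the two candidates is confirmed as suitable, no additional staff are needed.

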### Data Collection

2.12

Data items for collection are based on international reporting standards for DFU studies [41]. Data will be collected from the patient, electronic patient records or direct patient measurements and entered onto a paper case report form (CRF) (Table 2).

**TABLE 2 iwj70176-tbl-0002:** Sources of data.

	Patient reported	Medical records	Direct measurements/observation
Enrolment			
Eligibility log			X
Recruitment log			X
Informed consent			X
Allocation			X
Deliverability			
Adherence to treatment			X
Adherence to follow up			X
Intervention			
Treatment completed			X
Number of shockwaves			X
Time to deliver ESWT			X
Side effects of ESWT	X		X
Demographics			
Age	X		
Sex	X		
Ethnicity	X		
BMI	X	X	X
Smoking status	X		
Weekly alcohol intake	X		
Type of diabetes mellitus	X	X	
HbA1c		X	
Diabetes management	X	X	
Cardiovascular disease	X	X	
Respiratory disease	X	X	
Chronic kidney disease	X	X	
Surgical history	X	X	
Allergies	X	X	
Medications	X	X	
Antibiotic use	X	X	
Ulcer characteristics			
Site			X
Laterality			X
Ulcer age	X	X	
SINBAD score			X
WIfI stage			X
Foot deformity			X
DFU photograph			X
Area			X
Depth			X
ABPI			X
Absolute toe pressure			X
Time to assess DFU			X
Ulcer care			
Dressing(s) type	X	X	X
Offloading footwear	X	X	X
Sharp debridement	X	X	X
Other interventions	X	X	X
Quality of life			
EQ‐5D‐3L	X		
DFS‐SF	X		
Wound‐Qol‐14	X		
Healthcare use^a^			
Number of outpatient appointments	X	X	
Number of GP appointments	X	X	
Number of hospital admissions	X	X	
Length of stay	X	X	
Number of practice nurse appointments	X	X	
Number of district nurse appointments	X	X	
Number of podiatrist appointments	X	X	
Number of prescriptions	X	X	
Number of operations	X	X	
Ulcer healing			X
Adverse events	X	X	X
Qualitative interview	X		

Abbreviations: ABPI: ankle brachial pressure index; BMI: body mass index; DFS‐SF: diabetic foot ulcer scale—short form; DFU: diabetic foot ulcer; EQ5D5L: EuroQol 5‐dimensions 5‐levels; ESWT: extracorporeal shockwave therapy; GP: general practitioner; INBAD: site ischaemia neuropathy bacterial infection area and depth score; WIfI: wound ischaemia foot infection stage.

^a^
Taken from the patient healthcare resource use diary.

Data relating to participant demographics, the DFU, standard care and quality of life will be taken at baseline.

Data relating to the number of shockwaves delivered, time to deliver ESWT and side effects will be recorded at each intervention session.

DFU measurements, standard care, quality of life and health resource use will be measured after the third treatment and at 6‐, 12‐ and 24‐weeks post randomisation (Table 3). DFU will be measured using tape measure and probe at the longest axis in each dimension. Data on healing, recurrence, major lower limb amputation and death will be collected until 1 year post randomisation. Healing is defined as complete re‐epithelisation without eschar assessed 2 weeks apart by a blinded wound assessor. Recurrence is defined as a break in the epithelium at the same site of the DFU after healing has been confirmed.

**TABLE 3 iwj70176-tbl-0003:** Schedule of enrolment, interventions and assessments.

	Enrolment	Allocation	Post allocation								
			ESWT treatment session (high/low/placebo; session)			Face‐to‐ face follow‐up (weeks post randomisation)			Telephone follow up^a^ (weeks post randomisation)	DFU healed visit^b^ (weeks)	Follow up from routine medical records (years)
Time point	−1	0	1	2	3	6	12	24	2–24	1–24	1–10
Enrolment											
Eligibility log	X										
Recruitment log	X										
Informed consent	X										
Allocation		X									
Deliverability											
Adherence to treatment			X	X	X						
Adherence to follow up						X	X	X	X	X	
Intervention											
Treatment completed			X	X	X						
Number of shockwaves			X	X	X						
Time to deliver ESWT			X	X	X						
Side effects of ESWT			X	X	X						
Assessments											
Demographics											
Age			X								
Sex			X								
Ethnicity			X								
BMI			X								
Smoking status			X								
Weekly alcohol intake			X								
Type of diabetes mellitus			X								
HbA1c			X								
Diabetes management			X		X	X	X	X			
Cardiovascular disease			X								
Respiratory disease			X								
Chronic kidney disease			X								
Surgical history			X								
Allergies			X								
Medications			X								
Antibiotic use			X		X	X	X	X			
Ulcer characteristics											
Site			X								
Laterality			X								
Ulcer age			X								
SINBAD score			X								
WIfI stage			X		X	X	X	X			
Foot deformity			X								
DFU photograph			X		X	X	X	X		X	
Area			X	X	X	X	X	X			
Depth			X		X	X	X				
ABPI			X								
Absolute toe pressure			X								
Time to assess DFU			X								
Ulcer care											
Dressing(s) type			X		X	X	X	X			
Offloading footwear			X		X	X	X	X			
Sharp debridement			X		X	X	X	X			
Other interventions			X		X	X	X	X			
Quality of life											
EQ‐5D‐3L			X		X	X	X	X			
DFS‐SF			X		X	X	X	X			
Wound‐Qol‐14			X		X	X	X	X			
Health resource use											
Number of outpatient appointments					X	X	X	X			
Number of GP appointments					X	X	X	X			
Number of hospital admissions					X	X	X	X			
Length of stay					X	X	X	X			
Number of practice nurse appointments					X	X	X	X			
Number of district nurse appointments					X	X	X	X			
Number of podiatrist appointments					X	X	X	X			
Number of prescriptions					X	X	X	X			
Number of operations					X	X	X	X			
Ulcer healing					X	X	X	X	X	X	X
Adverse events			X	X	X	X	X	X	X	X	X
Qualitative interview	X^c^			X^d^	X^d^	X^d^	X^d^	X	X^d^	X^d^	

Abbreviations: ABPI: ankle brachial pressure index; BMI: body mass index; DFS‐SF: diabetic foot ulcer scale – short form; DFU: diabetic foot ulcer; EQ5D5L: EuroQol 5‐dimensions 5‐levels; ESWT: extracorporeal shockwave therapy; GP: general practitioner; SINBAD: site ischaemia neuropathy bacterial infection area and depth score; WIfI: wound ischaemia foot infection stage.

^a^
Every 2 weeks between finishing ESWT and the 24‐week follow‐up visit.

^b^
If the patient reports the ulcer is healed, repeated 2 weeks later to ensure the DFU remains healed.

^c^
If the eligible patient declines trial participation.

^d^
If the participant decides to withdraw from the trial before the 24‐week follow‐up visit.

Health‐related quality of life will be measured using EuroQol 5D‐5L (EQ‐5D‐5L), diabetic foot ulcer scale short form (DFS‐SF) and Wound‐Qol‐14. EQ‐5D‐5L will be used to aid economic evaluation of ESWT [42, 43, 44]. DFS‐SF is a disease‐specific validated tool that measures health‐related quality of life in participants with a DFU [45]. Wound‐Qol‐14 will be validated during the pilot RCT and is hypothesised to have a higher completion rate than DFS‐SF as it is shorter (14 items versus 29 items). The tool has been validated in a population with chronic wounds, which included patients with DFUs [46, 47].

Participants can withdraw from the intervention, F2F follow‐up, telephone follow‐up or completely withdraw from the trial. Consent will be sought to use of the data already collected and to continue collecting data from routine medical records. If a patient is lost to follow‐up, data will be collected from routine medical records.

For the qualitative study, data will be collected using semi‐structured in‐depth interviews guided by group specific topic guides, informed by previous research and clinical experience. Interviews will be conducted by the lead author, who is a female vascular surgery registrar with training in qualitative interviewing. The topic guides will contain a mix of open and focused questions and will be piloted prior to use. All interviews will be audio‐recorded using a digital voice recorder and transcribed verbatim. Transcription will be undertaken by the researcher for the first three interviews. Microsoft Office Word transcribe tool will be used to transcribe the subsequent recordings.

